**Any Readmissions**

Study participants and family members will be encouraged to contact study personnel to inform of any readmissions to hospital within the province. Admission records will be requested from admitting facility (if other than Health Sciences Center) to review the date of admission, cause of admission, duration of admission and diagnosis. Any medical or surgical adverse events will be noted on the appropriate Unscheduled Readmissions Form. Patients will be managed at the discretion of the treating physician.

## 7. Safety Assessments

Safety monitoring for this study will focus on unanticipated problems involving risks to participants, including unanticipated problems that meet the definition of a serious adverse event.

### **7.1 Unanticipated Problems**

Unanticipated problems involving risks to subjects or others to include, in general, any incident, experience, or outcome that meets all of the following criteria:

- unexpected in terms of nature, severity, or frequency given (a) the research procedures that are described in the protocol-related documents, such as the REB-approved research protocol and informed consent document; and (b) the characteristics of the subject population being studied;
- related or possibly related to participation in the research (possibly related means there is a reasonable possibility that the incident, experience, or outcome may have been caused by the procedures involved in the research); and
- suggests that the research places subjects or others at a greater risk of harm (including physical, psychological, economic, or social harm) than was previously known or recognized.

### **7.2 Serious Adverse Events**

A serious adverse event (SAE) is one that meets one or more of the following criteria:

- Results in death
- Is life-threatening (places the subject at immediate risk of death from the event as it occurred)
- Results in inpatient hospitalization or prolongation of existing hospitalization
- Results in a persistent or significant disability or incapacity
- Results in a congenital anomaly or birth defect

Any unanticipated or serious adverse events will be reported to the research ethics board as per the procedures documented in *Section 7.3 Reporting Procedures*.

### **7.3 Reporting Procedures**

Incidents or events that meet the criteria for unanticipated problems require the creation and completion of a serious adverse events form. Investigators will include the following information when reporting an adverse event, or any other incident, experience, or outcome as an unanticipated problem to the REB:

- appropriate identifying information for the research protocol, such as the title, investigator’s name, and the REB project number;
- a detailed description of the adverse event, incident, experience, or outcome;
- an explanation of the basis for determining that the adverse event, incident, experience, or outcome represents an unanticipated problem;
- a description of any changes to the protocol or other corrective actions that have been taken or are proposed in response to the unanticipated problem.

To satisfy the requirement for prompt reporting, unanticipated problems will be reported using the following timeline:

- Unanticipated problems that are serious adverse events will be reported to the REB within 1 week of the investigator becoming aware of the event.
- Any other unanticipated problem will be reported to the REB within 2 weeks of the investigator becoming aware of the problem.

### **7.4 Study Oversight**

The investigator will be responsible for study oversight, including monitoring safety, ensuring that the study is conducted according to the protocol and ensuring data integrity. The PI will review the data for safety concerns and data trends at regular intervals, and will promptly report to the research ethics board any Unanticipated Problem (UP), protocol deviation, or any other significant event that arises during the conduct of the study.

A safety monitoring committee will be convened to review all adverse events during the study. The safety monitoring committee will consist of the primary investigators, critical care physicians and neurosurgeons. The committee will review all adverse events for every cohort of 5 patients enrolled into the study. To ensure timely review of adverse events, the data safety monitoring committee will review adverse events within the first 30 days of the surgical and study interventions.

## 8. Statistical Considerations

### 8.1 General Statistics

Statistical analysis will be performed utilizing R statistical software (R Core Team (2018). R: A language and environment for statistical computing. R Foundation for Statistical Computing, Vienna, Austria. URL https://www.R-project.org/). Alpha for statistical significance will be set at 0.05, with normality for all continuous variables tested via Shapiro-Wilks test. Basic descriptive statistics will be performed, with comparison between groups and variables conducted via t-test, Mann-Whitney-U, chi-square, analysis of variance (ANOVA), Kruskal-Wallis, Friedman and Joncheere-Terpstra testing, where appropriate. General correlations will be described using Pearson/Spearman coefficients, where applicable.

Descriptive statistical analysis of the relationships between physiologic variables will be facilitated through various error bar plots, linear models, quadratic models (ie. For optimal SCPP determination) and locally weighted scatterplot smoothing (LOESS) techniques, depending on the physiologic relationship being assessed.

### 8.3 Association with Secondary Outcomes

ISP, MAP, SCPP, sAMP, sRAP and the spinal vascular reactivity indices will be evaluated in relationship to motor evoked potential recordings, and functional outcome measures at the defined time periods of assessment. Such analysis will involve linear and logistic regression modelling techniques, evaluating the relationship between the physiologic parameters with: ASIA, FIM and QLI-SCI functional outcome metrics.

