2. Prospectively evaluate the overall relationship between spinal cord perfusion pressure and functional outcomes in patients with acute traumatic spinal cord injury.
   1. HYPOTHESIS: There will be a general positive relationship between both SCPP and individual optimal SCPP, with patient functional outcome in acute traumatic spinal cord injury.
3. Evaluate the relationship between SCPP, motor evoked potentials and functional outcomes after *incomplete* spinal cord injury.
   1. HYPOTHESIS: Time spent with SCPP near individual optimal SCPP will be directly associated with improved motor evoked potentials and functional outcomes in *incomplete* spinal cord injury.

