### ***3.2* Study Outcome Measures**

*Primary Outcome Measures*

The outcome measures of interest for our primary objective and specific aims include monitoring of intraspinal pressure via a strain-gauge pressure transducing wire placed at the site of injury and the derivation of various spinal physiologic metrics (see section 4.1 in Study Design). We will focus on various signal processing techniques to derive: ISP, MAP, SCPP, sAMP, sRAP and various spinal cord vascular reactivity metrics during the post-acquisition processing phase of the study. This will allow for the evaluation of relationships between spinal physiologic metrics, as outlined in the specific aims for the primary objective.

*Secondary Outcome Measures*

Safety of intraspinal pressure monitoring will be measured based on the accuracy of placement of the probe from postoperative computed tomography (CT) scan imaging, as well as collection of adverse events including infection rates, rates of pseudomeningoceles, neurological injury, probe dislodgement, meningitis, and/or subdural hematoma at the site of probe placement.

Where functional outcomes are of interest, we will measure changes to the ASIA impairment scale, functional independence score (FIM) and Quality of Life Index for Spinal Cord Injury (QLI-SCI).

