## 4. Study Design

### **4.1 Patient Population**

This study will be a single-center observational study involving patients admitted to the intensive care unit at Health Sciences Centre with acute traumatic spinal cord injury (ASIA A, B or C). All patients will undergo placement of an intraspinal pressure monitor within 24hrs of arrival. Physiological recordings will occur during the SICU stay for a maximum duration of 5 days (or until discharge from the intensive care unit).

Given that this is a feasibility and validation study, we will recruit patients over 2 years and anticipate that 20 patients will be enrolled during this time frame. Upon admission, patients will be screened for inclusion in the study based on the inclusion and exclusion criteria listed in *Section 5*. Initial demographic information, medical history, physical examination and imaging findings will be recorded using standardized data collection forms for all patients that consent to participation in the study. Patients will then be taken for surgical intervention within 24hrs of admission, and an intraspinal pressure monitor will be inserted as part of the overall surgical procedure. Initial intraspinal pressure readings will be recorded intraoperatively. Standardized data collection forms will then be used to collect pertinent data related to the surgical intervention and any intraoperative adverse events. Similarly, postoperative adverse events will be collected for the first 30 days following surgical intervention.

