### ***4.3* Motor Evoked Potentials**

In patients undergoing evaluation for motor evoked potential monitoring, we will capture transcranial magnetic motor evoked potentials within the 24 hours pre-operatively, 24hrs post-operatively and again during the standardized functional assessments at 1, 3, 6, 9 and 12 months.

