***5.1 Inclusion Criteria***

In order to participate in this study, patients must meet all of the following criteria:

- patients with acute traumatic spinal cord injury ASIA A, B or C
- spinal vertebral level between C0-L1
- age between 18–70yrs

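### Section 8.3 gives the pre-operative motor evoked potential no role, although secondary objective 3 is about improvement and section 4.3 collects the starting value

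*Protocol*

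**What the plan says.** The hypothesis under secondary objective 3 (Protocol, Study Objectives) is limited to incomplete injury. It states that time near the patient's own optimal SCPP "will be directly associated with improved motor evoked potentials and functional outcomes".

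Section 4.3 supplies a starting value. In patients evaluated for MEPs, "we will capture transcranial magnetic motor evoked potentials within the 24 hours pre-operatively, 24hrs post-operatively", with further recordings at 1, 3, 6, 9 and 12 months. Section 6.2 adds MEP testing at the daily visits on post-operative days 1 to 5.

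Section 8.3 states that ISP, MAP, SCPP, sAMP, sRAP and the reactivity indices "will be evaluated in relationship to motor evoked potential recordings, and functional outcome measures at the defined time periods of assessment". It continues: "Such analysis will involve linear and logistic regression modelling techniques, evaluating the relationship between the physiologic parameters with: ASIA, FIM and QLI-SCI functional outcome metrics". That regression sentence lists three functional scales and does not list the MEP.

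Section 3.2 describes the functional scales in terms of change. It says nothing comparable for the MEP. No other section says how the pre-operative MEP is used.

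**The concern.** Improvement needs a starting value. The protocol collects one and then describes an analysis of recordings at time points, which is an analysis of MEP level. A patient whose MEP is larger before surgery will tend to have a larger one afterwards, whatever the perfusion pressure.

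This matters because SCPP is observed, not assigned. Section 4.2 defines it as MAP minus ISP. If a more damaged cord goes with a higher ISP, the damage lowers SCPP and, separately, lowers the MEP. The two would then be associated without any effect of perfusion. The MEP hypothesis also applies only to the incomplete injuries among an anticipated 20 patients, so one prognostic variable can decide the result.

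There is a smaller defect of wording as well. The assessment times in section 4.3 include the pre-operative recording. Section 4.1 has the probe inserted during surgery, so that recording precedes all monitored SCPP and cannot be an outcome of it.

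**Working it through.** The protocol gives no power, effect size or SD for this analysis, so there is no figure to reproduce. The following is an illustration.

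**Inputs from the protocol**
- Anticipated enrolment of 20 (section 4.1). The number with incomplete injury, or with MEPs, is not stated.
- Alpha of 0.05 (section 8.1), sidedness not stated.

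**Assumptions, not in the documents**
- A two-sided test, with n = 10 for the incomplete-injury subgroup and n = 20 as the upper limit.
- r, the correlation of pre-operative with post-operative MEP: 0.6 to 0.8, with 0.3 and 0.5 as checks.
- ρ, the correlation of pre-operative MEP with mean SCPP: 0.1 to 0.4.

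**Model.** All variables are standardised and normal. B is the pre-operative MEP, X = ρB + √(1−ρ²)·e₁ is SCPP, and Y = bX + rB + √(1−r²)·e₂ is the post-operative MEP. Rejection rates come from t-tests in simulated trials, at least 20,000 per setting.

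**Bias with no true effect (b = 0).** The slope of Y on X without B is r × ρ:
- ρ = 0.4: 0.6 × 0.4 = 0.24 and 0.8 × 0.4 = 0.32 SD per SD.
- ρ = 0.1: 0.6 × 0.1 = 0.06 and 0.8 × 0.1 = 0.08.

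False-positive rate without B, n = 10:

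| ρ | r = 0.6 | r = 0.8 |
|---|---|---|
| 0.1 | about 5.5% | about 5.5% |
| 0.2 | about 6% | about 7% |
| 0.4 | 10% | 15% |

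At n = 20 and ρ = 0.4 the rates are 17% and 28%. With r = 0.3, ρ = 0.4 and n = 10, the rate is about 6%. With B in the model the rate is about 5% and the slope about zero in every setting.

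**A simple change score does not settle it.** With b = 0, the slope of Y − B on X is (r − 1) × ρ. At ρ = 0.4 this is −0.4 × 0.4 = −0.16 and −0.2 × 0.4 = −0.08. Level, change and baseline-adjusted analyses therefore give different answers to the same question.

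**Precision.** The squared standard error, adjusted over unadjusted, is roughly (1−r²)/(1−ρ²):
- r = 0.6, ρ = 0: 0.64.
- r = 0.8, ρ = 0: 0.36.
- r = 0.6, ρ = 0.4: 0.64/0.84 = 0.76.
- r = 0.3, ρ = 0.4: 0.91/0.84 = 1.08, a loss.

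**Power at n = 10, ρ = 0, b = 0.6.** Unadjusted power is about 35%. Adjusted power is 33% to 34% at r = 0.3, about 39% at r = 0.5, 43% at r = 0.6 and 63% at r = 0.8. At r = 0.6, if 2 of the 10 patients lack a pre-operative MEP, adjusted power is 31%; if 3 lack it, 25%. Both are below the unadjusted 35%.

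**The case against.** Section 8.3 is silent on baseline; it does not prescribe an unadjusted model. It names no covariate for any outcome, and its regression sentence does not mention the MEP. A reader might infer that a regression of post-operative MEP on SCPP without baseline has been specified, but the text does not say so. The wording of the hypothesis and the scheduling of a pre-operative recording both point towards a baseline comparison, and covariates are commonly left to an analysis plan, which is not at hand here. All of this stands. What remains is a mismatch inside the protocol: the hypothesis is about improvement, the analysis section describes recordings at time points, and the starting value is collected without a use.

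The hypothesis also uses time near an individual optimum, whereas the mechanism and the illustration use mean SCPP. A higher SCPP is not the same as more time near the optimum. The figures therefore bear on the general SCPP–MEP association in section 8.3, and carry over to the time-near-optimum measure only if that too is related to initial damage.

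A reader might infer that power is being lost. The documents claim no power for this analysis, and the gain from adjusting needs r clearly above ρ and few missing baselines. Nor do the bias and power arguments simply add up. With ρ = 0.4 and b = 0.6 at n = 10, rejection falls on adjustment, from 59% to 38% (r = 0.6) and from 67% to 57% (r = 0.8). The unadjusted slopes there are 0.6 + 0.24 = 0.84 and 0.6 + 0.32 = 0.92, so part of the unadjusted rejection is bias.

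Finally, adjustment restores 5% in the illustration because the pre-operative MEP is the only confounder there and is measured without error. The data are also normal, whereas absent MEP responses would pile up at zero. Real data would be less tidy.

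**Conclusion.** The point holds as a gap between the hypothesis and the analysis section. Section 8.3 describes MEP level where the hypothesis concerns improvement, gives the collected pre-operative value no role, and leaves open that this value is treated as an outcome.

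The consequence is possible, not shown. It requires initial cord damage to be related to SCPP, and the documents give no figure for that. Under ρ of 0.1 to 0.4 and r of 0.6 to 0.8, the false-positive rate at an assumed n = 10 is about 5.5% to 15% instead of 5%; at the low end the distortion is negligible. The protocol does not support the reading that damage will be mistaken for a perfusion effect, nor that power is necessarily lost. This is a secondary analysis in a small feasibility and validation study. The case for the change rests on matching the analysis to the hypothesis and limiting bias, with precision as a possible extra.

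**What to change.** In section 8.3, state that:
1. any model with a post-operative MEP as outcome includes the same patient's pre-operative MEP as a covariate, in preference to a simple change score;
2. the pre-operative recording is a baseline and not an outcome time point;
3. the unadjusted estimate is reported alongside as a sensitivity analysis, with the number of patients in each fit, because the sample is small and baselines may be missing.

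The index coefficient is then read as an association with later MEP given the starting value.

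The cost is two or three sentences and no new data, since section 4.3 already schedules the recording. Each model loses one degree of freedom, and patients without a pre-operative MEP drop out of the adjusted fit. That loss may not be trivial: the recording has to be made before surgery that section 4.1 places within 24 hours of admission.

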## 9. Source Documents and Access to Source Data/Documents

Study staff will maintain appropriate medical and research records for this study, in compliance with institutional requirements for the protection of confidentiality of subjects. Study staff will permit authorized representatives of regulatory agencies to examine (and when required by applicable law, to copy) research records for the purposes of quality assurance reviews, audits, and evaluation of the study safety, progress and data validity.

Data recorded during the course of the study will be documented using clinical research forms or using digital software. Hard copies of study records will be archived by the investigator in a locked room located in the office of the PI in the Section of Neurosurgery at Health Sciences Center. Access to this room is monitored by hospital security and is limited to the primary investigator and one administrative assistant. When the office is not occupied, the door will be locked at all times. Study records will be destroyed after 25 years. All patient charts will be stored according to Manitoba Health policy. Computer access is through Manitoba eHealth who maintains a firewall. Each member of the study team has their own user ID number and terminals will be logged off when not being used.

Any disposal of documents will be destroyed by placing in confidential shredding bins located on the hospital premises. Publication/presentations will be done with aggregate data and no patient identifiers will be released.

### **9.1 Data Handling and Record Keeping**

The investigators are responsible for ensuring the accuracy, completeness, legibility, and timeliness of the data reported. All source documents should be completed in a neat, legible manner to ensure accurate interpretation of data. The investigators will maintain adequate case histories of study participants, including accurate case report forms (CRFs), and source documentation.

### **9.2 Data Management Responsibilities**

Data collection and accurate documentation are the responsibility of the study staff under the supervision of the investigator. All source documents and laboratory reports must be reviewed by the study team and data entry staff, who will ensure that they are accurate and complete. Unanticipated problems must be reviewed by the investigator or designee.

## 10 Ethics And Protection of Human Subjects

### **10.1 Research Ethics Board Submissions**

The protocol, informed consent form(s), recruitment materials and all participant materials will be submitted to the REB for review and approval. Approval of both the protocol and the consent form must be obtained before any participant is enrolled. Any amendment to the protocol will require review and approval by the REB before the changes are implemented in the study.

### **10.2 Informed Consent**

Informed consent will be obtained prior to the individual agreeing to participate in the study and will continue throughout study participation. Extensive discussion of risks and possible benefits of study participation will be provided to participants and their families. A consent form describing in detail the study procedures and risks will be given to the participant. Consent forms will be REB-approved, and the participant is required to read and review the document or have the document read to him or her. The investigator or designee will explain the research study to the participant and answer any questions that may arise. The participant will sign the informed consent document prior to any study-related assessments or procedures. Participants will be given the opportunity to discuss the study with their surrogates or think about it prior to agreeing to participate. They may withdraw consent at any time throughout the course of the study. A copy of the signed informed consent document will be given to participants for their records. The rights and welfare of the participants will be protected by emphasizing to them that the quality of their clinical care will not be adversely affected if they decline to participate in this study.

The consent process will be documented in the clinical or research record. If the patient is under the clinical care of the principal investigator for the study, then another member of the research team will become involved to obtain consent from the patient.

### **10.3 Patient Confidentiality**

Participant confidentiality is strictly held in trust by the investigators, study staff, and the sponsor(s) and their agents. This confidentiality is extended to cover testing of biological samples and genetic tests in addition to any study information relating to participants.

The study protocol, documentation, data, and all other information generated will be held in strict confidence. No information concerning the study or the data will be released to any unauthorized third party without prior written approval of the REB.

## Appendix 1 – Study Schedule

| Assessment | Screening Visit | Baseline Enrollment Visit | Surgical Treatment Visit | Intraspinal Pressure Monitoring Visit 1 | Intraspinal Pressure Monitoring Visit 2 | Intraspinal Pressure Monitoring Visit 3 | Intraspinal Pressure Monitoring Visit 4 | Intraspinal Pressure Monitoring Visit 5 | Postoperative In-hospital visits | Any Readmission | Follow Up Visit 1 (1 month after surgery | Follow up Visit 2 (3 months after surgery) | Follow Up Visit 3 (6 months After surgery) | Follow Up Visit 4 (9 months after surgery) | Follow Up Visit 5 (12 months after surgery) |
| --- | --- | --- | --- | --- | --- | --- | --- | --- | --- | --- | --- | --- | --- | --- | --- |
| Time Frame | Day 0 to 1 | Day 0 to 1 | Day 0 to 3 | POD#1 | POD #2 | POD #3 | POD #4 | POD#5 | POD#6-29 | Any Readmission | POD#30 | 3 months following surgery +/-14days) | 6 months following surgery +/-14days) | 9 months following surgery +/-14days) | 12 months following surgery +/-14days) |
| Screening Log |  |  |  |  |  |  |  |  |  |  |  |  |  |  |  |
| Confirmationation of Inclusion/Exclusion Criteria |  |  |  |  |  |  |  |  |  |  |  |  |  |  |  |
| Informed Consent |  |  |  |  |  |  |  |  |  |  |  |  |  |  |  |
| Initial Clinical Assessment |  |  |  |  |  |  |  |  |  |  |  |  |  |  |  |
| Medical History |  |  |  |  |  |  |  |  |  |  |  |  |  |  |  |
| Physical Examination |  |  |  |  |  |  |  |  |  |  |  |  |  |  |  |

| Assessment | Screening Visit | Baseline Enrollment Visit | Surgical Treatment Visit | Intraspinal Pressure Monitoring Visit 1 | Intraspinal Pressure Monitoring Visit 2 | Intraspinal Pressure Monitoring Visit 3 | Intraspinal Pressure Monitoring Visit 4 | Intraspinal Pressure Monitoring Visit 5 | Postoperative In-hospital visits | Any Readmission | Follow Up Visit 1 (1 month after surgery | Follow up Visit 2 (3 months after surgery) | Follow Up Visit 3 (6 months After surgery) | Follow Up Visit 4 (9 months after surgery) | Follow Up Visit 5 (12 months after surgery) |
| --- | --- | --- | --- | --- | --- | --- | --- | --- | --- | --- | --- | --- | --- | --- | --- |
| Time Frame | Day 0 to 1 | Day 0 to 1 | Day 0 to 3 | POD#1 | POD #2 | POD #3 | POD #4 | POD#5 | POD#6-29 | Any Readmission | POD#30 | 3 months following surgery +/-14days) | 6 months following surgery +/-14days) | 9 months following surgery +/-14days) | 12 months following surgery +/-14days) |
| Medications |  |  |  |  |  |  |  |  |  |  |  |  |  |  |  |
| Laboratory Investigations (Hematology and chemistry) |  |  |  |  |  |  |  |  |  |  |  |  |  |  |  |
| Vital Signs |  |  |  |  |  |  |  |  |  |  |  |  |  |  |  |
| Clinical and Radiographic Injury Classification |  |  |  |  |  |  |  |  |  |  |  |  |  |  |  |
| ASIA Impairment Scale |  |  |  |  |  |  |  |  |  |  |  |  |  |  |  |
| Functional Independence Measure |  |  |  |  |  |  |  |  |  |  |  |  |  |  |  |
| Assessment | Screening Visit | Baseline Enrollment Visit | Surgical Treatment Visit | Intraspinal Pressure Monitoring Visit 1 | Intraspinal Pressure Monitoring Visit 2 | Intraspinal Pressure Monitoring Visit 3 | Intraspinal Pressure Monitoring Visit 4 | Intraspinal Pressure Monitoring Visit 5 | Postoperative In-hospital visits | Any Readmission | Follow Up Visit 1 (1 month after surgery | Follow up Visit 2 (3 months after surgery) | Follow Up Visit 3 (6 months After surgery) | Follow Up Visit 4 (9 months after surgery) | Follow Up Visit 5 (12 months after surgery) |
| Time Frame | Day 0 to 1 | Day 0 to 1 | Day 0 to 3 | POD#1 | POD #2 | POD #3 | POD #4 | POD#5 | POD#6-29 | Any Readmission | POD#30 | 3 months following surgery +/-14days) | 6 months following surgery +/-14days) | 9 months following surgery +/-14days) | 12 months following surgery +/-14days) |
| Quality of Life Index for Spinal Cord Injury |  |  |  |  |  |  |  |  |  |  |  |  |  |  |  |
| Anesthesia Log |  |  |  |  |  |  |  |  |  |  |  |  |  |  |  |
| Intraoperative Intraspinal Pressure Monitoring Form |  |  |  |  |  |  |  |  |  |  |  |  |  |  |  |
| Intraoperative neurophysiological record form |  |  |  |  |  |  |  |  |  |  |  |  |  |  |  |
| Intraoperative adverse event form |  |  |  |  |  |  |  |  |  |  |  |  |  |  |  |
| ICU Physiological Recordings |  |  |  |  |  |  |  |  |  |  |  |  |  |  |  |
| Assessment | Screening Visit | Baseline Enrollment Visit | Surgical Treatment Visit | Intraspinal Pressure Monitoring Visit 1 | Intraspinal Pressure Monitoring Visit 2 | Intraspinal Pressure Monitoring Visit 3 | Intraspinal Pressure Monitoring Visit 4 | Intraspinal Pressure Monitoring Visit 5 | Postoperative In-hospital visits | Any Readmission | Follow Up Visit 1 (1 month after surgery | Follow up Visit 2 (3 months after surgery) | Follow Up Visit 3 (6 months After surgery) | Follow Up Visit 4 (9 months after surgery) | Follow Up Visit 5 (12 months after surgery) |
| Time Frame | Day 0 to 1 | Day 0 to 1 | Day 0 to 3 | POD#1 | POD #2 | POD #3 | POD #4 | POD#5 | POD#6-29 | Any Readmission | POD#30 | 3 months following surgery +/-14days) | 6 months following surgery +/-14days) | 9 months following surgery +/-14days) | 12 months following surgery +/-14days) |
| ICU Intraspinal Pressure Recordings |  |  |  |  |  |  |  |  |  |  |  |  |  |  |  |
| Neurophysiological Monitoring Report |  |  |  |  |  |  |  |  |  |  |  |  |  |  |  |
| Spinal Cord Injury – Secondary Complications Form |  |  |  |  |  |  |  |  |  |  |  |  |  |  |  |
| Unscheduled Readmissions Form |  |  |  |  |  |  |  |  |  |  |  |  |  |  |  |
| Postoperative Medial Adverse Events |  |  |  |  |  |  |  |  |  |  |  |  |  |  |  |

| Assessment | Screening Visit | Baseline Enrollment Visit | Surgical Treatment Visit | Intraspinal Pressure Monitoring Visit 1 | Intraspinal Pressure Monitoring Visit 2 | Intraspinal Pressure Monitoring Visit 3 | Intraspinal Pressure Monitoring Visit 4 | Intraspinal Pressure Monitoring Visit 5 | Postoperative In-hospital visits | Any Readmission | Follow Up Visit 1 (1 month after surgery | Follow up Visit 2 (3 months after surgery) | Follow Up Visit 3 (6 months After surgery) | Follow Up Visit 4 (9 months after surgery) | Follow Up Visit 5 (12 months after surgery) |
| --- | --- | --- | --- | --- | --- | --- | --- | --- | --- | --- | --- | --- | --- | --- | --- |
| Time Frame | Day 0 to 1 | Day 0 to 1 | Day 0 to 3 | POD#1 | POD #2 | POD #3 | POD #4 | POD#5 | POD#6-29 | Any Readmission | POD#30 | 3 months following surgery +/-14days) | 6 months following surgery +/-14days) | 9 months following surgery +/-14days) | 12 months following surgery +/-14days) |
| Postoperative Surgical Adverse Events Report |  |  |  |  |  |  |  |  |  |  |  |  |  |  |  |
| Protocol Violation Report |  |  |  |  |  |  |  |  |  |  |  |  |  |  |  |
| Physical Therapy and Rehabilitation Form |  |  |  |  |  |  |  |  |  |  |  |  |  |  |  |
| Close Out Letter to Patient |  |  |  |  |  |  |  |  |  |  |  |  |  |  |  |

